**C. Immunogenicity study**

A list of children to participate in the immunogenicity study will be generated by WLVP and will include subjects who have received either the conjugate vaccine or placeboat any one of the study sites. One nurse will be specifically responsible for obtaining blood specimens from the appropriate children; therefore, for logistical reasons, only children who have received all 3 doses of the vaccine/placebo at the same clinic will be eligible for the immunogenicity study. As there is no scheduled clinic visit at 18 weeks, the informed consent will be given to the parents at the 14 week visit. To ensure that blood is taken from appropriate numbers of children given either placebo or conjugate vaccine, the study identification numbers of children initially randomized into the immunization study who, for any reason, are not bled, will be sent to WLVP. A list of alternate children will then be generated.

Approximately 2 ml of blood will be taken by finger stick at 18 weeks, 4 weeks after the third immunization. The blood will be collected in a red tube and then the sera will be removed after clotting and centrifugation and stored at -70oC.

**D. Assessment of vaccine safety**

1. All children will be observed for 15 minutes following vaccine administration for any immediate local and/or systemic reactions at the clinic by qualified study personnel. Parents will also be advised to return to the clinic immediately should the child develop reactions of concern to the parent. Follow-up will occur on all allergic reactions, severe local reactions within 72 hours of vaccination, as well as on all seizures occurring within 4 weeks of vaccination.

2. The study pediatricians will conduct daily surveillance for hospitalization of study children (see Section VIII) at Chris Hani Baragwanath Hospital. All deaths, life-threatening events, and unexpected events related to the vaccine will also be investigated. Efforts will also be made to follow-up all deaths occurring outside of the hospital through death notifications and cemetery records. Prior to implementation of the study, meetings will be held with the pediatricians of the hospitals to inform them of the nature of the study and the need to notify study investigators should they see study participants. Reminder notices will be placed in the appropriate wards and the children’s Road to Health cards will also be clearly labelled so as to indicate their participation in the study. The majority of mothers bring the Road to Health card when the child is hospitalized.

3. The Safety Monitoring Committee (see Section XIV) and WLVP will review safety data quarterly during the trial. All severe, life-threatening reactions or the deaths of study participants, regardless of the etiology, and unexpected events felt by the study physicians to be vaccine-related will be reported monthly to the members of the Committee as well as to WLVP. Quarterly reporting to WLVP will include all of the above reactions as well as seizures or changes in neurological status within one month of vaccination and severe local or systemic reactions or allergic reactions within 72 hours of vaccination. A report of the incident cases of pneumococcal disease will be provided to the Safety Committee quarterly.

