**D. Contraindications for subsequent doses of the study vaccine**

1. An immediate anaphylactic or any other serious reaction to a prior dose of study vaccine.

2. Child is withdrawn from the study at the request of the parent/guardian, or as a recommendation from the Safety Monitoring Committee.

3. Development of a progressive neurological or seizure disorder.

4. Contraindications specified in the manufacturers’ package insert for DTP/Hib vaccine [TETRAMUNE ®, Appendix 5]

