**D**. **Treatment period**

Each study subject will receive three injections of either pneumococcal conjugate vaccine or placebo, administered concurrently with TETRAMUNE®, OPV, and Hep B. The injections will be administered at approximately 6, 10, and 14 weeks of age, with a minimum interval of 3 weeks between each dose and all three doses must be completed by 9 months of age. Children not returning within 1 week of the appointed time for the second or third vaccinations will either be telephoned or visited at home.

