**X. Adverse reactions**

The results of the Phase II trial assessing the safety and immunogenicity of the nonavalent pneumococcal conjugate vaccine, which is presently being concluded at Zola clinic, will be available soon. Preliminary data from 500 children suggest the vaccine to be well-tolerated. No serious adverse reactions were recorded. During the proposed efficacy study all children will be monitored for 15 minutes after vaccination for any signs or symptoms of adverse reactions. Resuscitation facilities will be available at all the health centers. All signs or symptoms will be recorded on an Adverse Reaction Form as well as on the Road to Health card.

Parents will also be advised to watch for signs and symptoms of local reactions, including erythema, swelling, induration and/or tenderness at the site of vaccination and for systemic reactions, such as difficulty with breathing, drowsiness, vomiting and fever lasting for greater than 24 hours. Parents will be instructed to bring their children to the clinic/hospital immediately for medical assessment and/or management for any vaccine event of concern.

Parents/guardians will be asked to request doctors/nurses not directly involved with the study to note any event requiring medical attendance on their Road to Health card, including the clinical diagnosis and treatment given. The Road to Health card, which is usually safeguarded by the parent/guardian, will be reviewed at each vaccination visit. The card will also be reviewed by the admitting physician should the child require hospitalization.

Any patient experiencing a serious clinical adverse reaction will have a detailed history, physical examination and appropriate laboratory procedures done by a study pediatrician. All deaths, life-threatening events, and all unexpected vaccine-related events will also be investigated. These events will be reported to the Safety Monitoring Committee and WLVP monthly.

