**A. Safety**

Vaccine safety will be monitored and reported as described in Section XI. Safety will be analyzed as the trial progresses, with reports on adverse reactions and outcome cases provided to the Safety Monitoring Committee on a quarterly basis. Deaths, life-threatening events, and unexpected events judged to be vaccine-related will be reported to the Committee monthly. All serious adverse events will be investigated.

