**XIV. Rules for unblinding the study**

The randomization code will be broken:

A. For reasons of safety or excess mortality, as determined by the Safety Monitoring Committee. In the event of a serious adverse reaction following vaccination, the code may be broken for individual children. The identity of the randomization group may be provided to the child’s parents, physician, and to the study Investigator, if deemed necessary by the Safety Monitoring Committee. The Committee also has the authority to unblind the trial and recommend to the IAC that the trial be terminated should safety issues warrant such action.

B. For reasons of lack of vaccine efficacy. Outcome cases of pneumococcal disease will be unblinded and reviewed quarterly by the Safety Monitoring Committee. The Committee will be provided with estimates of the number of cases in each vaccine group that would be required to consider the vaccine without efficacy. The Safety Monitoring Committee may recommend to the International Advisory Committee that the trial be terminated, based on their findings.

C.Upon completion of enrollment and follow-up of study participants and termination of the trial.

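### Life-threatening and unexpected vaccine-related events go to the Safety Monitoring Committee on a monthly cycle with no expedited route, so a report can arrive after the child's next dose

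*Protocol*

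**What the plan says.** Three protocol sections set the same reporting cycle.

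- VI.D item 3 covers severe or life-threatening reactions, deaths from any cause, and unexpected events that study physicians think vaccine-related. These "will be reported monthly to the members of the Committee as well as to WLVP".
- Section X covers deaths, life-threatening events and unexpected vaccine-related events: "These events will be reported to the Safety Monitoring Committee and WLVP monthly".
- XII.A names only the SMC. It says that deaths, life-threatening events and "unexpected events judged to be vaccine-related will be reported to the Committee monthly".

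Review is slower still: "The Safety Monitoring Committee (see Section XIV) and WLVP will review safety data quarterly during the trial" (VI.D item 3).

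On dosing, V.D says: "The injections will be administered at approximately 6, 10, and 14 weeks of age", "with a minimum interval of 3 weeks between each dose".

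The SMC has three powers that depend on its knowing of an event.

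- A child may be withdrawn from later doses at the parent's request "or as a recommendation from the Safety Monitoring Committee" (IV.D item 2).
- Under XIV.A, "In the event of a serious adverse reaction following vaccination, the code may be broken for individual children", and the SMC judges whether the allocation is passed to the parents, physician and investigator.
- Under IX.G the SMC may conclude that a safety concern should end the trial.

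None of the three carries a notification time.

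**The concern.** The powers and the reporting flow are set in different sections and do not fit together. Staff at the clinics and the hospital are blinded. The code is held by an SMC member and by one person at the manufacturer outside the trial (V.C). Unblinding a child after a serious reaction is useful mainly if it is quick, yet the only report that must reach the code-holders runs on a monthly cycle. A recommendation to withdraw a child matters only if it comes before the next dose, and that dose may be due sooner than the report. The same delay applies to recognising a vaccine-related pattern across clinics, which no single clinic can see.

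The protocol does make information move fast at the local level: parents contact the investigator at once if the child is hospitalised (V.F.1), and study pediatricians survey admissions daily (VI.D item 2). It does not carry that speed on to the SMC.

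**Working it through.** The protocol states no figure to reproduce. The check compares the reporting cycle with the dose gap.

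**Inputs**
- Reporting cycle: monthly (VI.D item 3, X, XII.A), M = 365.25/12 = 30.4 days.
- Review cycle: quarterly (VI.D item 3), Q = 365.25/4 = 91.3 days.
- Scheduled dose gap: 10 − 6 = 14 − 10 = 4 weeks, g = 28 days (V.D).
- Minimum dose gap: 3 weeks, g = 21 days (V.D).

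**Assumptions, not stated in the protocol.** Reports go out on a fixed date each month. An event falls at random within the cycle, staff learn of it on the day, and the next report includes it. No time is added for the SMC to read and respond.

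**Step 1: length of the wait.** It runs from 0 to 30.4 days, with mean 30.4/2 = 15.2 days. The mean is shorter than either dose gap; the maximum is longer than both.

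**Step 2: chance that the report follows the next dose.** For an event d days after a dose, P = 1 − (g − d)/M.

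| Event day d | g = 28 | g = 21 |
| --- | --- | --- |
| 0 | 1 − 28/30.4 = 8% | 1 − 21/30.4 = 31% |
| 3 | 1 − 25/30.4 = 18% | 1 − 18/30.4 = 41% |
| 7 | 1 − 21/30.4 = 31% | 1 − 14/30.4 = 54% |

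For events spread evenly over the first week, P averages 19.5% (28 days) or 42.5% (21 days). The report therefore comes before the next dose in about 80% or 58% of such cases. The formula applies to events after doses 1 and 2 only, since nothing follows dose 3. When the next dose is given late, g is larger and P falls; for a vaccination-day event it reaches zero once the gap exceeds 30.4 days.

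**Step 3: if the SMC acts only at quarterly review.** For a vaccination-day event, P = 1 − 28/91.3 = 69%, or 1 − 21/91.3 = 77%. This is an outer bound, because members receive the monthly reports in between.

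**Step 4: search for a faster route.** XVI.B requires prompt reporting to the manufacturer, but it sits under protocol revisions, concerns emergencies and the procedures then used, and does not mention the SMC. XIII.B leaves the SMC's specific responsibilities to a later amendment and its review intervals to its members. That could bring faster notification, but nothing shown does so, and the monthly flow is fixed elsewhere.

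**The case against.** The strongest reply is that the child who reacted does not depend on the SMC. A serious reaction to an earlier dose is itself a contraindication to later ones (IV.D item 1), a medical assessment precedes every dose (VI.B item 1), and a study pediatrician works up serious reactions (X). This stands in full. A reader might infer that a child could be revaccinated after a serious reaction because the SMC had not yet heard of it; the protocol does not support that. These safeguards do not, however, inform the code-holders, enable unblinding, or show a pattern across clinics.

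Second, a monthly schedule does not forbid an earlier call, and XIV.A does not tie code-breaking to the reporting cycle. This also stands, but it leaves a safety power to initiative where the protocol has otherwise laid down a rule.

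Third, the three reporting sections agree with one another. That is right: the mismatch is between the reporting flow and the powers.

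Some stronger readings should be set aside.

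- That the SMC's powers always come too late: the mean wait is about 15 days, and most first-week events would be reported before the next dose.
- That the SMC is the last to hear: VI.D and X put the manufacturer on the same monthly cycle, and the International Advisory Committee receives quarterly progress summaries (XII.B).
- That the delay can be costed by counting all injections given meanwhile: this assumes that the whole birth cohort enrols and that one report would halt all dosing. The protocol does not say the latter.
- That every death within four weeks of a dose needs urgent reporting: the four-week window in VI.D item 1 is for seizure follow-up. Three such windows cover about 12 weeks per child. If the 670 deaths a year in IX.F were spread evenly, that would be 670 × 12/52 = about 155 deaths a year.

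**Conclusion.** The point holds in a limited form. The protocol fixes a monthly flow to the SMC in three places and gives no expedited route, while granting the SMC child-level and trial-level powers that need timely knowledge. A report can arrive after the next dose: about 8% to 31% of vaccination-day events and 31% to 54% of day-7 events, across the 28-day and 21-day gaps. These figures rest on a fixed report date and random event timing. They also allow no time for the SMC to respond, so the delay to action would be longer.

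What is exposed is timely individual unblinding, SMC-recommended withdrawal and early recognition of a trial-level safety signal. Clinic-level protection of the child who reacted is not. Efficacy estimates and power are not affected. This is a cheap improvement.

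**What to change.** In VI.D item 3, X and XII.A, add expedited notification to the SMC code-holder and the manufacturer, for example within 24 hours of study staff becoming aware. The 24 hours is a suggestion, not a protocol figure. Apply it to:

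- serious or life-threatening reactions, including deaths, that study physicians judge vaccine-related; and
- unexpected vaccine-related events.

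Keep the monthly list for all other deaths and keep the quarterly review. Reconcile IV.D item 2 and XIV.A with these three sections, so that each SMC power refers to the report that triggers it. The amendment announced in XIII.B could carry the wording. Clinical decisions on individual children stay under the existing rules.

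The cost is protocol wording and some added reporting work for study pediatricians, who already see the hospital cases daily. Because the trigger is a judgement that the event is vaccine-related, most of the roughly 670 expected deaths a year should stay on the monthly list.

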**E. Assessment of vaccine efficacy**

**1. Identification of study participants admitted to hospital** **with possible infectious disease etiology**

All pediatric patients under 2½ years of age, adjusted for the duration of time the study has been in progress, will be screened upon arrival in the admission ward to determine whether the patient has been enrolled in the study. The admission ward will be staffed on a 24-hour basis by qualified nursing assistants, who will interview the escort of the child to determine if the child is resident in the study area and has been recruited in the study. This information will be verified by reviewing the child’s Road to Health card. If the card is not immediately available, the escort will be requested to bring the card at his/her next visit. Further confirmation of study participation will be done through the central database. The name of the child, the date of birth, address, and mother’s name will be obtained from escorts of all admitted patients within the study age range. This information will be sent to the data management center for cross-checking with the central database of all study participants.

To ensure that all hospitalized study participants are assessed by study physicians, the register in each admitting ward will be reviewed daily for any children within the appropriate age range. Escorts of these children will be interviewed as described above.

All patients will have a Case Information Form completed after being assessed by a study physician; forms from patients identified as study participants will be sent to the data management center. All efforts will be made, however, to blind the study physicians to the vaccination code of the cases. Study physicians will not see the Road to Health cards. Case Information Forms from non-study patients will be stored separately and will be cross-checked with the central database for a period of two weeks. This is to ensure that children whose forms may have been delayed in reaching the data management center or not have been immediately entered into the database are not misclassified as non-study participants.

Further surveillance by study physicians will include follow-up of all patients in the pediatric wards from whom *S. pneumoniae* has been isolated from a normally sterile body site, as reported by the hospital microbiology laboratory. Case Information Forms, etc will be completed and verified as described above.

**2. Investigation of hospitalized study-patients**

**a. Routine investigations**

Investigations will be determined by the clinical presentation of the child; however, the following tests are routine:

* full blood count

* blood culture

* C- Reactive-protein

* Chest X-ray if pneumonia/septicaemia is suspected

* Lumber puncture for cerebro-spinal fluid analysis if meningitis is suspected

* Other test/s as recommended by the attending pediatrician

**b. Additional tests that are specific to the study**

A total of 2-3 ml of serum will be collected in a red tube for pneumococcal antibody titer testing; antibody titers will be performed concomitantly at SAIMR and/or at WLVP using standardized ELISA tests.

A second blood specimen of 2 ml will be taken in an EDTA (purple) top tube for HIV testing. All clotted blood will be stored refrigerated and clarified by centrifugation within 24 hours after collection at the central SAIMR laboratory. Approximately 0.6 ml of clarified serum will be transferred into 1.0 ml tubes and labeled with the appropriate patient identity. All sera will be stored in a -70oC freezer. HIV ELISA testing will be performed on serum from those children who were not tested during hospitalization. The serum will be renumbered and linked to non-identifying features eg, number of doses received, age at time of disease, nature of disease, etc. To confirm HIV positive status, HIV PCR will be performed on all serum found to be ELISA positive in the hospital as well as during the testing at SAIMR. Children with HIV ELISA positive/PCR negative serum will be considered to be HIV-uninfected.

**c. Microbiology methods**

Isolates of *S. pneumoniae* will be identified by standard microbiological techniques at the microbiology laboratory of the hospital to which the patient has been admitted, i.e., the microbiology laboratories at Chris Hani Baragwanath Hospital. Serotyping/serogrouping of pneumococci will be performed using both the Quelling and latex reactions at the MRC/SAIMR/Wits/Pneumococcal Diseases Research Unit. Antibiotic susceptibility testing will be performed using the disc diffusion method. Minimum Inhibitory Concentrations (MICs) will be determined using the microdilution method for those isolates that show resistance by the disc diffusion method.

**VII. Vaccines and vaccine management**

**A. Nonavalent pneumococcal conjugate vaccine**

The nonavalent conjugate vaccine is manufactured by WLVP. Each 0.5 ml. dose contains 2 g each of polysaccharide belonging to serotypes 1, 4,5, 9V, 14, 19F and 23F; 2g of oligosaccharide of serotype 18C; and 4 g of 6B polysaccharide. All the polysaccharides are independently coupled to a total of approximately 20 g of CRM 197 (a non-toxic mutant of diphtheria toxoid) that acts as a protein carrier.

**B. ‘Control’ vaccine**

Patients in the control group will receive a placebo injection that is identical in appearance to the nonavalent pneumococcal conjugate vaccine. The placebo will be prepared by WLVP and will contain sucrose, the stabilizer for the pneumococcal conjugate vaccine.

**C. Other vaccines administered at 6, 10 and 14 weeks**

All children will receive TETRAMUNE®, manufactured by WLVP, and Hep B (Hepacine, Cheil Sugar Organization, Korea) and OPV (Polioral trivalent, Biocine, Italy), which are the routine vaccines given to children in South Africa.

**D. Management of study vaccines**

Study vaccines will be shipped from the manufacturer to SAIMR in Johannesburg, South Africa. The vaccine will be locked in a secure storage facility and temperature control of this facility will be ensured. Vaccines will be brought by courier to the health centers involved in vaccination, where storage, safe-keeping and dispensing of the vaccine will be the responsibility of the study nurse. Daily recording of refrigerator temperature will be conducted and logs of the vaccine doses given each day will also be kept. The principal investigator and/or one of his appointees as well as WLVP monitors will oversee the management of the study vaccines. Comprehensive accounting will allow tracking of all vaccine doses from initial receipt to dispensing at the facilities.

**VIII. Case definition**

**A. Determination of efficacy against vaccine serotype invasive pneumococcal disease in HIV-uninfected children**

To be included in the first primary efficacy calculations the case must meet the following criteria:

* Have *S. pneumoniae* of a vaccine serotype isolated from a sterile body fluid, defined as blood, cerebrospinal fluid, pleural fluid, ascitic fluid, and synovial fluid, 14 days or more after the third dose of study vaccine.

* Have been vaccinated according to the protocol (see Section VI).

* Not have acquired or congenital immunodeficiency syndromes (HIV negative status determined by PCR for those with a positive HIV ELISA).

* Be the first episode of invasive pneumococcal disease of any serotype.

